# A factorial-design cluster randomised controlled trial investigating the cost-effectiveness of a nutrition supplement and an exercise programme on pneumonia incidence, walking capacity and body mass index in older people living in Santiago, Chile: the CENEX study protocol

**DOI:** 10.1186/1475-2891-6-14

**Published:** 2007-07-05

## Abstract

**Background:**

Chile is currently undergoing a period of rapid demographic transition which has led to an increase in the proportion of older people in the population; the proportion aged 60 years and over, for example, increased from 8% of the population in 1980 to 12% in 2005. In an effort to promote healthy ageing and preserve function, the government of Chile has formulated a package of actions into the *Programme of Complementary Feeding for the Older Population *(PACAM) which has been providing a nutritional supplement to older people since 1998. PACAM distributes micronutrient fortified foods to individuals aged 70 years and over registered at Primary Health Centres and enrolled in the programme. The recommended serving size (50 g/day) of these supplements provides 50% of daily micronutrient requirements and 20% of daily energy requirements of older people. No information is currently available on the cost-effectiveness of the supplementation programme.

**Aim:**

The aim of the CENEX cluster randomised controlled trial is to evaluate the cost-effectiveness of an ongoing nutrition supplementation programme, and a specially designed physical exercise intervention for older people of low to medium socio-economic status living in Santiago, Chile.

**Methods:**

The study has been conceptualised as a public health programme effectiveness study and has been designed as a 24-month factorial cluster-randomised controlled trial conducted among 2800 individuals aged 65.0–67.9 years at baseline attending 28 health centres in Santiago. The main outcomes are incidence of pneumonia, walking capacity and change in body mass index over 24 months of intervention. Costing data (user and provider), collected at all levels, will enable the determination of the cost-effectiveness of the two interventions individually and in combination. The study is supported by the Ministry of Health in Chile, which is keen to expand and improve its national programme of nutrition for older people based on sound science-base and evidence for cost-effectiveness.

**Trial registration:**

ISRCTN48153354

## Background and rationale

United Nations estimates show that in 2000, individuals aged 60 years or older represented 10% of the world's population, or about 600 million people, and they project that by the year 2050 this group will represent 22% of the world's population, or about 2 billion people. Furthermore, the population of individuals aged 80 years or older is projected to more than triple in the period 2000–2050, from 1.2% to 4.3% of the world's population, or about 73 million to 400 million people [1]. These changes will be most dramatic in the less developed countries in Asia and Latin America, where the population age structure will change rapidly from one that is predominantly young, with relatively low proportions of older people, to one with more balanced numbers across age groups. Promoting good health in later life is desirable whatever the demographic context, but the growing proportions of older people make this particularly important now, especially in low and middle income countries with limited resources to devote to the care of older people in poor health. At the 2^nd ^World Assembly on Ageing, policy initiatives were proposed to promote active and healthy ageing [2]. Emphasis was placed on adequate nutrition throughout the life course and national food policies designed to recognise older people as potentially vulnerable.

Current evidence suggests that adherence to a healthy lifestyle, including a Mediterranean-style diet high in micronutrients, and moderate levels of physical activity is associated with considerably enhanced survival chances in later life [3]. The benefits of micronutrients may well arise from their role in maintaining immune competence, and micronutrient supplementation has been demonstrated to reverse some changes associated with impaired immunity in older people [4]. The evidence from the few clinical trials currently available provide mixed results [5]. Physically active people have a healthier and longer life [6], and a lack of physical exercise in older age is associated with a higher mortality rate [7]. A recent Cochrane review of randomised trials of strength training among older people found that training had a large positive effect on strength and also had a modest effect on functional measures such as gait speed and timed chair rise [8]. Markers of physical function such as gait speed also appear to be associated with cognitive function in older age [9].

Chile has undergone a period of rapid demographic transition which has led to an increase in the proportion of older people in the population: the proportion aged 60 years and over, for example, increased from 8% of the population in 1980 to 12% in 2005. In an effort to promote healthy ageing and preserve health and function, the government of Chile has formulated a package of actions into the *Programme of Complementary Feeding for the Older Population *(PACAM) which has been providing a nutritional supplement, rich in micronutrients, to older people since 1998. PACAM distributes micronutrient fortified foods to individuals 70 years and over registered at Primary Health Centres and enrolled in the programme. Since mid-2005, beneficiaries of the programme have been receiving 1 kg of *Años Dorados *every month, which provides 400 kcal/100 g, as well as a large array of micronutrients, and 1 kg of *Bebida Láctea*, a micronutrient fortified milk-based drink. The recommended serving size (50 g/day) of these supplements provide 50% of daily micronutrient requirements and 20% of daily energy requirements of older people [10,11].

One of the stated aims of the nutritional supplement is to improve micronutrient status of older people and thus enhance health status, potentially via the actions of micronutrients on immune function. Policy makers and user groups in Chile have suggested that PACAM would be enhanced by the inclusion of a regular programme of physical activity [12]. These combined actions may well be extremely important as older people in Chile suffer from high rates of respiratory infections [13] and pneumonia is the largest cause of death in people over 80 years in Chile [14]. Furthermore, according to the 2003 National Health Survey, 95.7% of the Chilean population over 64 years of age have a sedentary lifestyle [15].

The aim of the CENEX study is to assess whether nutritional supplementation and physical exercise can improve the health and well-being of older people and prevent disease and functional disability. Specifically, the project aims to determine whether a nutrition and exercise intervention will prevent pneumonia and preserve walking capacity among community-living older people of low to medium socio-economic status in Santiago, Chile. The project will also collect information on all costs borne by both the providers and beneficiaries of the interventions, in order to determine cost-effectiveness. The study will serve to examine the programme as currently implemented, inform policy debate on the need to add an exercise component, and provide essential cost-effectiveness information on two simple interventions aimed at improving the health and physical function of older people.

## Methods

### Design

The nutritional supplements are distributed to older people at health centres, and the study is therefore designed as a factorial cluster-randomised controlled trial of the effect of a two year intervention consisting of either a nutritional supplement, or a resistance training exercise programme, or both, or neither, on the incidence of pneumonia, walking capacity and body mass index among adults aged 65.0–67.9 years at baseline living in low to medium socio-economic status areas of Santiago, Chile. The procedures are illustrated schematically in Figures 1 and 2, and detailed in the text. On the assumption of no important interactions between the two interventions on the primary outcomes, the study aims to test three primary hypotheses.

**Figure 1 F1:**
[figure not shown]
Flow chart of CENEX Chile protocol for original 20 clusters.

**Figure 2 F2:**
[figure not shown]
Flow chart of CENEX Chile protocol for additional 8 clusters collecting data for pneumonia outcome only.

### Study hypotheses

Provision at health centres of a micronutrient fortified nutritional supplement for 24 months to adults aged 65.0–67.9 years at baseline will decrease the incidence of pneumonia among the group of individuals to whom access to the supplement is offered.

Provision of a community-based, twice-weekly resistance training exercise programme for 24 months to adults aged 65.0–67.9 years at baseline will increase walking capacity among individuals to whom access to the programme is offered.

Provision of a food supplement providing 20% of daily energy needs in conjunction with an exercise programme for 24 months to adults aged 65.0–67.9 years at baseline will not induce weight gain as measured by body mass index.

### Cluster inclusion criteria

• Health centre in Santiago Metropolitan area

• Situated in low-middle socio-economic status municipality

• More than 400 individuals in age-group 65.0–67.9 years resident in municipality

### Participant inclusion criteria

• Resident within catchment area of selected health centres

• Age 65.0–67.9 at baseline

• Potential national health service (FONASA) beneficiary

### Participant exclusion criteria

• Inability to walk unaided

• Having sought medical advice for an un-planned weight loss of 3 kg in the past 3 months

• Planning to move house in the next 3 months

• Being currently enrolled in PACAM or being current consumer of Años Dorados and/or Bebida Láctea

• Poor cognitive health (defined low score on cognitive health screen)

### 1. Recruitment of health centres (clusters)

#### Original health centre recruitment plan

This pragmatic trial was designed as a public health programme effectiveness study [16] and the interventions were therefore made available through the established health system under standard operating procedures, without the use of resource-intensive extraordinary efforts to secure uptake.

There are 94 health centres in the Santiago Metropolitan area. The study is aimed at low to medium socio-economic status older people, and the nine health centres in high socio-economic status municipalities were therefore excluded. The average number of persons aged 65.0–67.9 per health centre was derived from 1992 census data for each municipality, and small municipalities (those with less than 400 persons of this age group per health centre) were excluded (n = 49) in order to facilitate data collection.

The geographic catchment areas of the remaining 36 health centres in low to medium socio-economic status areas with sufficient older persons were mapped, and following further discussions and site inspections, 15 health centres were excluded because of insufficient interest among health centre staff (self-perception of having heavy burden of work), or infrastructure limitations, for example lack of space to store the nutritional supplement, or no private room to conduct the interviews. Of the 21 remaining health centres, 20 were randomly assigned, using stratified random sampling, to one of the four treatment arms. The remaining health centre was kept in reserve in the event of the withdrawal of a health centre.

#### Revised health centre recruitment plan

Following the change to the sample size requirement outlined below [see *Revised sample size calculations for the nutrition intervention (PACAM)*], which required a further 8 clusters to be included, the reserve health centre and the 15 health centres originally excluded were reconsidered for participation in the study. An additional eight health centres agreed to take part and could support the limited data collection required (see *Data collection among additional eight clusters*). The eight health centres were randomly assigned, using stratified random sampling, to either the nutrition intervention arm or the control arm of the trial.

### 2. Recruitment of participants

Following the random assignment of the selected health centres to one of the four trial arms, project field staff initiated the recruitment of potential participants living in the health centre catchment areas. Households within the selected catchment areas, randomly sampled from detailed maps of city blocks, were visited by project field staff, and all potentially eligible older people within selected households were identified. Potential participants were aged 65.0–67.9 years at baseline: individuals in this age-group are currently not eligible to receive PACAM.

A team of 20 project field staff initiated the process of randomly sampling houses in the selected clusters on 4th May 2005, and after two months the team had sampled more than 6000 houses and managed to identify 601 potentially eligible individuals. Of these, 351 individuals stated that they were willing to attend a further appointment, the majority of the remainder stated that they had no time (65%) or no interest (35%). Of the 351 individuals expressing an interest, 242 were recruited to the study. The concomitant availability of 2002 census data made it clear that adults aged 65–67.9 were spread thinly and were also unevenly geographically distributed in the selected clusters. It was therefore decided that a new sampling strategy within clusters was required. The revised recruitment strategy was based on the gathered evidence which indicated that 95% of those who had been identified as potentially eligible via the random sampling procedure, were also on health centre registries. It was therefore agreed that the names of older people on registries held in health centres would be used as the basis for recruitment.

Potential participants identified by either of these strategies received, on contact, an information sheet outlining the nature and importance of the study, and were asked for contact details. The information sheet explicitly stated which intervention the potential participant would receive on providing consent to join the study. This method of randomising clusters prior to identifying participants has been shown to result in potential recruitment bias [17], and extra efforts, such as demonstrations by health workers and public meetings at the health centres were made to ensure that acceptance rates in the four study arms were comparable.

Potential participants were then contacted by telephone, or in person, by a member of the project field staff a minimum of two days after receiving the information sheets. If the potential participant expressed an interest in the study, they were asked if they were ambulatory (being able to walk independently and thus complete the physical assessment required for the exercise intervention), if they had sought medical advice due to unexplained weight loss of greater than 3 kg in the past three months (which may suggest an underlying pathology), or if they intended to move house (to a different health centre catchment area) within the next three months. Individuals who report that they were non-ambulatory, and/or had sought medical advice due to unexplained weight loss, and/or intended to move within the next three months were not invited to take part in the study and were thanked for their time and co-operation.

Remaining potential participants were invited to attend an appointment at a local community centre. Individuals who were unable to attend the appointment at the community centre but remained interested in the study were visited at their homes by a member of the project field staff. Potential participants were assured (as stated on the information sheet) that if they did not wish to take part in the study, it would not prejudice the quality of health care provision from their health centre. In addition, potential participants on health centre registries were invited to informal group meetings to receive information about the study.

At the baseline appointment (approximately one week later), potential participants were provided with detailed information sheets and fully informed by the project field staff about the nature and relevance of the trial, and exactly what will be involved if they agreed to take part. Potential participants were then asked to give consent to undergo a brief cognitive screen, a short version of the Mini Mental State Examination (MMSE). The MMSE is an easy to administer test that has been widely validated as a screen for dementia [18], and was used to exclude participants with low cognitive status. Participants with an MMSE short-version score of less than 13 (out of a maximum of 19), suggesting possible cognitive impairment, were further assessed using the 11-item Pfeffer screen [19]. Potential participants scoring six or greater in the Pfeffer screen were not included in the study, as a short-form MMSE score of less than 13 combined with a Pfeffer screen score of six or greater has been validated in Chile as a marker for possible dementia in adults [20]. Individuals with an MMSE short version score below 13 and a Pfeffer screen score of 6 or greater were thanked for their time and co-operation.

Potential participants who were not excluded for possible dementia were invited to consent to take part in the study. Individuals unwilling to participate further were thanked for their time and co-operation. Individuals giving informed consent were enrolled in the trial.

All consenting participants were then first assessed by completing questionnaires in their local community centre or their homes. They were then invited to attend a local community centre where they underwent anthropometric assessment, blood pressure measurement and two brief mobility tests (see *Data Collection*). The baseline assessment took approximately 90 minutes to complete and the anthropometric assessment, blood pressure measurement and mobility tests took approximately 30 minutes to complete for participants from the original 20 clusters. It took approximately 45 minutes to collect the limited data required for the pneumonia outcome in the additional eight clusters. At this time, participants were informed about health care provision at their local health centre and the potential benefits of registration with the National Health Service. Participants were given contact details for the study manager, and thanked for their time and co-operation.

### Interventions

A variety of study outcomes have been identified which could plausibly be influenced by the interventions. Since it cannot be assumed that the effects of these two interventions will be additive in all cases, a factorial design with four distinct study arms is required. The four study arms are: i. Nutrition intervention (PACAM) alone, ii. Exercise alone, iii. Nutrition plus exercise and, iv. Control.

### Nutrition intervention (PACAM)

PACAM was made available to participants aged 65.0–67.9 years at baseline who lived within the defined catchment area of the selected health centres. The programme was provided in its current form as delivered by the Ministry of Health. The primary products of PACAM are the nutritional supplements *Años Dorados *(a cereal-legume and vegetable powdered food) and *Bebida Láctea *(a milk-based powdered drink), 1 kg of each of which is distributed to all eligible individuals every month at the health centre. Detailed nutritional composition of the dietary supplements is provided in Table 1. Compliance with the nutrition intervention is assessed by recording the frequency of collection of the supplements from the health centres, and via specific questions asked at the 12 and 24 month interviews.

**Table 1 T1:** Nutritional composition of the *Años Dorados *and *Bebida Láctea *food supplements used in the Programme for Complementary Food in Older People, Chile, 2007

	**Años Dorados**		**Bebida Láctea**	
	per 100 g	per 50 g serving	per 100 g	per 25 g serving
Energy (kcal)	400	200	406	101.5
Protein (g)	13.0	6.5	18.0	4.5
Total fat (g)	11.0	5.5	10.0	2.5
Carbohydrates (g)	62.3	31.1	61.0	15.3
Total fibre (g)	6.0	3.0	1.0	0.25
				
**Vitamins/minerals**				
Vitamin A (μg RE)	240.0	120.0	800.0	200.0
Vitamin C (mg)	30.0	15.0	180.0	45.0
Vitamin D (μg)	8.0	4.0	16.0	4.0
Vitamin E (mg TE)	16.0	8.0	32.0	8.0
Vitamin B_1 _(mg)	0.4	0.2	0.8	0.2
Vitamin B_2 _(mg)	0.4	0.2	1.6	0.4
Niacin (mg NE)	4.5	2.3	10.0	2.5
Vitamin B_6 _(mg)	1.0	0.5	1.6	0.4
Folate (μg)	100.0	50.0	400.0	100.0
Vitamin B_12 _(μg)	1.4	0.7	2.8	0.7
Sodium (mg)	280.0	140.0	540.0	135.0
Calcium (mg)	400.0	200.0	1000.0	250.0
Iron (mg)	4.2	2.1	5.6	1.4
Phosphorus (mg)	400.0	200.0	800.0	200.0
Magnesium (mg)	150.0	75.0	300.0	75.0
Zinc (mg)	3.0	1.5	12.0	3.0

Abbreviations: RE – retinol equivalents; TE – alpha-tocopherol equivalents; NE – niacin equivalents

### Exercise intervention

Participants were individually invited to attend two physical activity group training sessions per week of one hour each. Training, supervised by CENEX study physical activity instructors, consists of a period of warming up and three levels of chair stands, three levels of modified squats, three levels of step-ups onto a stair, and six sets of 15 repetitions of arm pull-ups using rubber bands of variable resistance. Special exercises were delivered to participants with specific physical limitations. Participants were encouraged to walk to the exercise classes (up to 20 minutes from home) as part of the exercise protocol. Participants unable to attend classes were advised about exercises that could be conducted in their homes. Compliance with the exercise intervention is assessed by recording the frequency of attending the training sessions, and via specific questions asked at the 12 and 24 month interviews.

### Nutrition plus exercise intervention

Eligible participants received both the nutritional supplement and were invited to attend the exercise intervention as outlined above.

### Control group

Participants in the control group received neither the nutritional supplement nor were they invited to attend the exercise intervention. They were however, provided with the same level of general support and information as all other study participants and also underwent identical assessments as all other study participants throughout the study period.

At the end of the study, all study participants will receive educational material on healthy ageing and a certificate in recognition of their participation.

## Outcome measures

### Primary outcomes for nutrition intervention (PACAM)

The incidence of pneumonia over the 24 months after the initiation of the intervention.

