### Data collection at 24 months in the original 20 clusters

A final evaluation of all study participants will be carried out after 24 months of intervention. Study participants will be invited to their local community centre, or visited in their homes, and assessed for:

1. Selected socio-demographic characteristics and productive social activity: as at baseline.

2. Depression: GDS15 as at baseline.

3. Self-reported health status: SF36 as at baseline.

4. Cognitive function: as at 12 months.

5. Self-reported presence of medically-diagnosed diseases: as at baseline.

6. Self-reported hospitalization: as at baseline.

7. Self-reported incidence of falls or fractures in the previous 12 months.

8. Self-reported medications currently being taken on a daily basis: as at baseline.

9. Self-reported health service utilization: as at baseline.

10. Compliance with the interventions: as at 12 months.

All participants will then be given an appointment to attend a local community centre where the following information will be collected by project field staff:

1. Anthropometry: as at baseline.

2. Blood pressure measurement: as at baseline.

3. Timed up-and-go: as at baseline.

4. 6 minute walk: as at baseline.

Information on incidence of pneumonia will be collected for 24 months of intervention (including two winter seasons); after this, routine clinic information on pneumonia incidence will be collected on study participants for a further 6 months.

The sub-sample of 120 participants per study arm will be asked for new blood samples collected under fasting conditions, as at baseline.

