### Data collection among additional eight clusters

Following identical recruitment and screening procedure to that undergone by participants in the original 20 clusters, individuals from the additional eight clusters who provide consent to take part in the study will undergo baseline assessment at their local community centre or in their home. Given the late initiation of this additional sample, participants in the additional eight clusters were enrolled for 18 months. Information on incidence of pneumonia will therefore be collected for 18 months of intervention (including two winter seasons); after this, routine clinic information on pneumonia incidence will be collected on study participants for a further 6 months. The following selected data will be collected at baseline:

1. Basic sociodemographic and economic characteristics

2. Self-reported health status: SF36

3. Self-reported medications currently being taken on a daily basis.

4. Self-reported incidence of, and treatment for, pneumonia within the previous 12 months

5. Self-reported smoking and drinking habits

6. Anthropometry: weight, height and hand-grip strength.

7. Blood pressure measurement: two measurements under sitting conditions separated by five minutes, using a sphygmomanometer.

Ambulatory and hospitalized cases of pneumonia among participants in the additional eight clusters will be identified in an identical manner to that described for the original 20 clusters.

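### The primary pneumonia outcome is set at 24 months for all 28 clusters, but the eight added clusters get 18 months of intervention, and neither the window nor the person-years is reconciled

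*Protocol article*

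**What the plan says.** All places are in the protocol article.

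- **Outcome.** Under *Primary outcomes for nutrition intervention (PACAM)*: "The incidence of pneumonia over the 24 months after the initiation of the intervention". No cluster is excepted.
- **Hypothesis.** Under *Study hypotheses*: "Provision at health centres of a micronutrient fortified nutritional supplement for 24 months". The Abstract likewise describes a 24-month trial in 2800 people.
- **Sample size.** *Revised sample size calculations for nutrition intervention (PACAM)* targets a 33% reduction in 2-year incidence. With 14 clusters per arm it counts 200 person-years per cluster, as 100 participants followed for 2 years, in all 28 clusters.
- **Added clusters.** Under *Data collection among additional eight clusters*: "participants in the additional eight clusters were enrolled for 18 months", because they started late. Pneumonia is collected for 18 months of intervention, and "after this, routine clinic information on pneumonia incidence will be collected on study participants for a further 6 months".
- **Original clusters.** *Data collection at 24 months in the original 20 clusters* has the parallel arrangement: 24 months of intervention, then 6 months of routine data. Both periods are said to include two winters.
- **Allocation.** Under *Revised health centre recruitment plan*: "The eight health centres were randomly assigned, using stratified random sampling, to either the nutrition intervention arm or the control arm". The original 20 centres had been randomised earlier, to four arms.

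**The concern.** The eight clusters were added only for the pneumonia outcome (caption of Figure 2), yet they are the ones that do not fit its definition. Two readings remain open.

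- **Literal 24 months.** The last quarter of the window in these clusters follows the stated 18 months of intervention and rests on routine clinic information.
- **Intervention period only.** Follow-up is 18 months in eight clusters and 24 in twenty. A 2-year incidence is then not the quantity measured in the eight, and the person-years in the sample size section are too high.

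The readings give different estimands, person-time and power. While the text is silent, the primary window could be chosen after the data are seen. Also, 18 months and 24 months each contain two winters, so the expected rate per person-year differs between the two sets of clusters by design.

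**Working it through.** **Inputs.** From the revised sample size section: 28 clusters of 100, 14 per arm, 2 years, 33% reduction, 80% power, p < 0.05 (sidedness not stated; two-sided assumed here), virtually no loss to follow-up. From the data collection sections: 24 months of intervention in 20 clusters and 18 in 8. Of the 14 clusters per arm, 10 come from the original 20, so 4 come from the added 8.

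**1. The plan's own figure.** 100 × 2 = 200 person-years per cluster; 14 × 200 = 2800 per arm; 28 × 200 = 5600 in total. This person-time arithmetic reproduces.

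The statement that 200 gives 80% power does not reproduce. Five hospitalised cases per 1000 (read as per year) and a 5:1 ratio give rates of 0.030 and 0.030 × 0.67 = 0.0201. The usual rate formula without clustering is (0.0501 × 2.80²)/(14 × 0.0099²), about 287 person-years per cluster two-sided; one-sided it gives about 226. The present point does not depend on this. Below, 80% at 200 is taken as given.

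**2. Person-time on intervention.** Added clusters: 100 × 1.5 = 150 each.

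- Total: 20 × 200 + 8 × 150 = 5200.
- Per arm: 10 × 200 + 4 × 150 = 2600.
- Ratio: 5200/5600 = 0.929, a loss of 7.1%.

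**3. Power on that person-time.** Scaling the stated 80% by the square root of person-time: 2.80 × √0.929 − 1.96 = 0.74, and Φ(0.74) = 77%. Adding between-cluster variation (coefficients of 0.125 and 0.18 tried) gives 76.6% to 76.9%.

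**4. Season.** *Recruitment status* dates second-wave recruitment from 10 March to 2 June 2006. If intervention started at recruitment (assumption), month 18 falls between about September and December 2007, and months 18 to 24 run to about March to June 2008, largely outside winter. Suppose 5% to 15% of a cluster's 24-month events fall in those months (assumed range). Dropping them costs 8/28 × 5% to 15% = 1.4% to 4.3% of events. Power is then Φ(2.80 × √0.986 − 1.96) = 79% down to Φ(2.80 × √0.957 − 1.96) = 78%.

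**5. Counting months 18 to 24 instead.** Let f be the share of 24-month events in those months, and assume no effect after month 18. The reduction in the eight clusters is 0.33 × (1 − f). Overall it is (20 × 0.33 + 8 × that)/28. Power is Φ(2.80 × overall/0.33 − 1.96).

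| f | Eight clusters | Overall | Power |
|---|---|---|---|
| 0.25 (flat rate) | 24.8% | 30.6% | 74% |
| 0.15 | 28.1% | 31.6% | 76% |
| 0.05 | 31.4% | 32.5% | 79% |

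**The case against.** The article is open about the 18 months and the reason for it. The parallel wording for the two sets of clusters suggests that the extra 6 months is post-intervention follow-up in both. *Data analysis* places the primary analyses at the end of the interventions, and the sample size is counted in person-years, which can accommodate unequal follow-up. On that view one clarifying sentence is missing. Much of this stands: the intervention-period reading is the more natural one. But that sentence is absent, the outcome definition contradicts that reading, and 200 person-years in every cluster is wrong under it.

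A reader might go further in four ways that the documents do not support.

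- **That the outcome cannot be measured in the eight clusters.** It can: 18 months plus 6 months of routine data make 24, and centralised registration is said to leave virtually no loss.
- **That the shorter window biases the comparison.** The second wave was randomised to nutrition or control, and 14 per arm implies 4 and 4, so both arms are shortened alike.
- **That the effect is heavily diluted.** The flat-rate result of about 31% is the unfavourable end. Two winters lie inside the first 18 months, and that months 18 to 24 are off intervention is implied rather than stated.
- **That controls in the original clusters become eligible for the programme at 70 during their extra 6 months.** That period is after month 24, outside the primary window on either reading.

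The choice of model and covariates can be left to the analysis plan and is not criticised here.

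**Conclusion.** The contradiction is real and concerns the primary outcome: 24 months in its definition, the hypothesis and the sample size, against 18 months of intervention in 8 of 28 clusters (28.6%), with nothing to reconcile them. The stated person-time is wrong for the intervention period, at 5600 rather than 5200.

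The practical size is modest. Power is about 77% on person-time, or 78% to 79% if few events fall in the missing months. It is 74% to 79% if months 18 to 24 are counted and the effect ends with the supplement. All these figures accept the stated 80% at 200 person-years per cluster; the seasonal shares and the immediate loss of effect are assumptions. What is at fault is an ambiguous estimand and a small, unacknowledged loss of power. This should be corrected, but it does not threaten the validity of the comparison between arms.

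**What to change.** 1. Define the primary outcome as the pneumonia rate per person-year over the intervention period: 24 months in the original 20 clusters and 18 months in the added 8, with person-time as the denominator.
2. Make the comparison within randomisation wave, because the waves were randomised separately and have different windows and seasonal mixes.
3. Assign the 6 months after the intervention, in both sets of clusters, to secondary analysis.
4. In the revised sample size section, restate person-time as 150 per added cluster, 2600 per arm and 5200 in total, with the power that follows. Amend the statements that imply 24 months for all 2800 participants.

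The cost is wording and a recalculation. No new data are needed and no treatment changes. It should be done before outcome data are seen by arm.
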